### Aims of the study

In the second phase of BEST (BEST-2) the primary question will be: ‘Is daily oral azithromycin non-inferior (within a 20% margin) to oral amoxycillin-clavulanate at achieving resolution of exacerbations by day 21 of treatment?’

The secondary aims are similar to those in BEST-1 [32], and are to: 1) determine the effect of azithromycin or amoxycillin-clavulanate on QOL, systemic inflammation, time to next respiratory exacerbation, and duration of exacerbations; 2) examine factors that predict response to the two antibiotics, including respiratory pathogens (viruses, bacteria, macrolide-resistant bacteria) present in respiratory secretions, and systemic markers of inflammation; and 3) describe, by using sensitive molecular detection techniques, the point prevalence and diversity of respiratory viruses and *Mycoplasma pneumoniae* and *Chlamydiales* species during exacerbations, compared with the findings at enrolment when the children are clinically stable.

The study will test the primary hypothesis that oral azithromycin is non-inferior (within a 20% margin) to oral amoxycillin-clavulanate at achieving resolution of respiratory exacerbations by day 21 of treatment in children with non-CF bronchiectasis.

## Methods

### Study design

We are conducting a multicenter, parallel group, double-dummy, double-blind placebo RCT (with concealed allocation) to assess whether oral azithromycin is non-inferior to oral amoxycillin-clavulanate at treating children with a non-severe exacerbation of bronchiectasis. Our study plan is summarized in Figure 1.

**Figure 1 F1:**
[figure not shown]
**Overall schematic study design.** Amox-clav, amoxycillin-clavulanate; Azithro, azithromycin; BEST, Bronchiectasis Exacerbation Study.

### Eligibility

The inclusion criteria are: age less than 19 years at time of enrolment; diagnosis of bronchiectasis by a respiratory physician following high-resolution computed tomography in the 5 years immediately prior to study entry, or if diagnosed earlier, evidence of regular follow-up by a respiratory physician for treatment of bronchiectasis; and more than two respiratory exacerbations in the 18 months prior to study entry. Children who have participated in BEST-1 [32] may participate subsequently in BEST-2. These children will be re-randomized for BEST-2.

Exclusion criteria are: current or recent severe exacerbation of bronchiectasis (dyspnea, hemoglobin desaturation <90% in air or hospitalization) in the 8 weeks immediately prior to study entry; presence of CF or liver dysfunction; hypersensitivity to beta-lactam or macrolide antibiotics; current or recent (in the 4-months before study enrolment) lower-airway infection by a member of the *Pseudomonas* genus of gram-negative bacteria; receipt of beta-lactam or macrolide antibiotics within the 3 weeks preceding study entry; or current treatment for cancer.

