### Intervention and follow-up

A double-dummy design is planned. If eligibility is fulfilled, and after informed consent has been obtained, the child will be randomized to one of two arms. At the start of the exacerbation, the child will receive orally: 1) azithromycin with placebo amoxycillin-clavulanate or 2) amoxycillin-clavulanate with placebo azithromycin. The azithromycin dose is 5 mg/kg/day (to a maximum of 200 mg daily, and for amoxycillin-clavulanate it is 22.5 mg/kg/dose twice daily (maximum 900 mg/dose). Equivalent volumes of placebo will be given for both trial medications. All treatments will continue for 21 days.

An exacerbation is defined as an increase in sputum volume or purulence, or change in cough (>20% increase in cough score [46] or type (dry to wet) [47]) for more than 3 days. We validated this definition in our prospective study, and found that the kappa values (between clinicians) of these symptoms and signs were excellent (>0.75) [48]. Daily diaries will also be collected during exacerbations until the scores for 2 or more days reflect the child’s baseline state, which for each child will be established at enrolment, prior to any exacerbations. This assessment consists of a combination of symptoms (daily cough (yes/no), cough quality (wet/dry/none), cough score [46] averaged over two consecutive days) and signs (sputum color (if any present) using a color chart card (BronkoTest Ltd, London, UK), and crackles on chest auscultation). Children will be reviewed on days 14 and 21, and at resolution of the exacerbation. The exacerbation is considered resolved when symptoms and signs are the same as the baseline state. Post-exacerbation, the children will be followed up and evaluated clinically every 3 months for a period of 18 months or until their next exacerbation (whichever is sooner). The time to next exacerbation will be determined by duration of days from the resolution of the current exacerbation to the beginning of the next exacerbation.

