### Randomization, allocation, and blinding

Upon enrolment, the child will be assigned to the next unique number on the appropriate stratified list. The allocation will be performed by the trial pharmacist at the Royal Children’s Hospital (Brisbane, Australia). Randomization is stratified by site (Brisbane, Darwin, Melbourne, Perth, Sydney, Auckland), age (≤5 or >5 years) and underlying etiology (idiopathic/post-pneumonia or all other causes). The randomization sequence is computer-generated and uses permuted blocks. The allocation sequence will be concealed at all times throughout the study. The computer-generated allocation sequence was prepared by a statistician external to the study team.

The specially manufactured placebo medications (Institute of Drug Technology Australia Ltd, Melbourne, Victoria, Australia), have a similar taste and color to their respective antibiotics. Both active medications (azithromycin and amoxycillin-clavulanate) will be repackaged and relabeled so that both antibiotics and their respective placebos are provided in identical opaque bottles. For all trial medications, equal volumes of water are added using a syringe and needle by punching the seal. Adherence will be assessed by parent report and return of empty bottles.

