#### Secondary clinical outcomes

The main secondary outcome is the PC-QOL score. Other outcomes are 1) the time to next exacerbation; 2) requirement for hospitalization; 3) duration of exacerbation (persistence of symptoms till return to baseline state); and 4) FEV_1_ % predicted.

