### Sample size

We plan to enroll 170 children (85 per arm), providing 90% power (α = 0.05, 1-sided) with 20% non-inferiority margin to detect 80% resolution rate by day 21. The margin selected is relatively large in statistical terms, but the physicians considered it clinically appropriate. As the primary outcome will be obtained in all enrolled children, retention fraction has not been factored in for the intention-to-treat analysis.

The main secondary outcome (secondary aim 1) is PC-QOL. Based on a non-inferiority limit of 0.9 (minimum important difference [57]) and standard deviation of 0.9, our sample size provides a power of 99.9% (α = 0.05, one-sided 95% CI) for data from at least 136 children (assuming at least 80% retention of children enrolled). For secondary aim 2 (see list under ‘Aims of the study’), we will be examining eight main factors, and thus a sample size of 136 exceeds the recommended minimum (n = 10 per factor) [65]. The eight factors are: smoking, age, underlying etiology, detection of virus (any versus none, then single versus multiple viruses), presence of azithromycin resistance, and levels of various blood markers (IL-6, IL-10, IP-10).

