#### Statistical analysis for secondary outcomes and aims

For the clinical secondary outcome (secondary aim 1), the *t*-test or the Mann–Whitney test will be used for continuous variables (depending on normality of data distribution). A Kaplan-Meier curve will be constructed for each group for time to resolution and time to next exacerbation, as reported previously [67]. For secondary aim 2 (factors that predict response to antibiotics), univariate analyses will be used to examine several biologic factors (for example, smoking, age, ethnicity, underlying etiology, detection of virus (any versus none, then single versus multiple viruses), presence of azithromycin resistance, and levels of blood markers (IL-6, IL-10, IP-10)). Factors with *P*<0.2 will be included in a logistic regression model. Potential interactions (for example,. between viruses and bacteria) will be examined in the model. Descriptive data will be used for secondary aim 3 (point prevalence of respiratory pathogens).

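### Time to next exacerbation has only an unadjusted Kaplan-Meier curve per arm as its stated analysis; a Cox estimate adjusted for prior exacerbation count would be a cheap, modest improvement

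*Protocol article*

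**What the plan says.** All references are to the protocol article.

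- **Eligibility** sets a threshold on history: "more than two respiratory exacerbations in the 18 months prior to study entry". It does not say that the exact number is recorded. The enrolment items under **Data collection** include prior illness, but no exacerbation count is named.
- **Aims of the study** places time to next exacerbation in secondary aim 1. **Secondary clinical outcomes** lists it after the main secondary outcome, PC-QOL: "Other outcomes are 1) the time to next exacerbation".
- **Intervention and follow-up** starts the clock at resolution of the treated exacerbation and reviews children "every 3 months for a period of 18 months or until their next exacerbation".
- **Statistical analysis for secondary outcomes and aims** gives this method: "A Kaplan-Meier curve will be constructed for each group for time to resolution and time to next exacerbation". It refers to an earlier report for the format. It names no test, effect estimate or covariate for this outcome.
- **Randomization, allocation, and blinding** stratifies by site (six centres), and by "age (≤5 or >5 years) and underlying etiology (idiopathic/post-pneumonia or all other causes". Prior exacerbation count is not a stratum.
- **Sample size** plans 170 children, 85 per arm. It gives power for the primary outcome and for PC-QOL, but none for time to next exacerbation.

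**The concern.** The entry window and the follow-up window are both 18 months, and both concern the same kind of event. A child's prior count is therefore a direct, if noisy, measure of that child's underlying rate of the outcome, and would be expected to be among the strongest baseline predictors of it.

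Two things follow. A Kaplan-Meier curve per arm is a display; without a hazard ratio and interval, the reader cannot say how large a difference between the antibiotics the data support or exclude. And a comparison that ignores large differences in rate between children is less efficient than one that uses them. The trial was not sized for this outcome, so efficiency is worth having.

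The data-collection part is time-sensitive. If the forms record only that the threshold was met, a later analysis plan cannot recover the count from them.

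**Working it through.** **No figure to reproduce.** The protocol gives no power, event number, exacerbation rate or hazard ratio for this outcome. Everything numerical below except the 170 children, the allocation, the strata, the entry threshold and the 18 months is an assumption.

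**Step 1: is an unadjusted comparison invalid?** With 85 per arm, the standardised difference in prior count between arms has SD √(2/85) = 0.153. In 95% of randomisations it therefore lies within ±1.96 × 0.153 = ±0.30 SD. For a 50:50 split of the count, the corresponding range is ±1.96 × √(0.25 × 2/85) = ±15 percentage points. Under no treatment effect, the simulated type I error of the unadjusted Cox test, without stratifying on the count, was 4.9% to 6.5%. The nominal level is 5% and the simulation standard error is √(0.05 × 0.95/1500) = 0.6 points. The comparison is essentially valid; what is at stake is precision.

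**Step 2: power with and without the count.** Assumptions: 170 children, 1:1; child-specific rates gamma-distributed; prior counts Poisson; entry only if the count exceeds 2; exponential time to next event at the same underlying rate; 18 months of follow-up; no dropout; hazard ratio 0.65; two-sided 5%; 1,500 runs per setting. A smaller shape means children differ more. The mean is before selection.

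| Shape | Mean per 18 months | Events | Unadjusted power | Adjusted for log(count) | Gain (points) |
|---|---|---|---|---|---|
| 1 | 3 | 157 | 57.2% | 65.9% | 8.7 |
| 1 | 5 | 162 | 54.6% | 68.3% | 13.7 |
| 2 | 3 | 156 | 59.5% | 65.1% | 5.6 |
| 2 | 5 | 163 | 61.0% | 70.7% | 9.7 |
| 4 | 3 | 155 | 63.7% | 67.3% | 3.6 |
| 4 | 5 | 163 | 67.0% | 71.8% | 4.8 |

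As a benchmark, if all children had the same rate, Schoenfeld's formula gives power Φ(√(d/4) × |ln 0.65| − 1.96). With d = 155 events this is Φ(6.225 × 0.4308 − 1.96) = Φ(0.72) = 76.5%. Adjustment recovers part of the gap, not all of it.

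**Step 3: a smaller sample.** With 136 children (170 × 0.8, the retention that the protocol assumes for PC-QOL), hazard ratio 0.6 and mean 2 to 4:

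- shape 1: about 58–63% rises to 69–71%
- shape 2: about 64–69% rises to 69–73%
- shape 4: about 68–72% rises to 69–75%

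The gain is 1 to 13 points. A separate simulation at the same sample size and hazard ratio gave about 1 to 11 points.

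**Step 4: imperfect history.** The settings above assume an error-free count and an unchanged rate. Both are optimistic. Past episodes need not have been counted by the trial's exacerbation definition, and children are enrolled when stable and treated at a later exacerbation. With 136 children, mean 3, and gains listed for shapes 1, 2 and 4:

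- perfect count: 8.6, 3.6 and 1.9 points
- log-SD 0.5 for rate change and 0.3 for count error: 5.9, 3.5 and 1.4 points
- log-SD 0.7 and 0.5: 3.0, 2.0 and 0.2 points

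These error sizes are also assumptions.

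**Step 5: would stratifying have done the job?** Splitting the count at its median in the randomisation, but analysing unadjusted, changed power by −0.9 to +4.1 points in the Step 2 settings, close to simulation noise. The existing strata already give 6 × 2 × 2 = 24 cells, or 170/24 ≈ 7 children each. A further two-level factor gives 48 cells of about 3.5.

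**The case against.** The strongest reply is that this is a condensed protocol article, and that covariates for a lesser secondary outcome are commonly left to an analysis plan. The stated curve is a display that follows an earlier report not available here; nothing rules out an adjusted model. That largely stands. It is why this is a suggested improvement to the one method the article names, and not a finding of error. It does not cover the recording of the count, which has to be settled when data are collected.

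It is also fair that the simulations assume a constant superiority hazard ratio over 18 months after a 21-day course, in a non-inferiority trial. The upper gains are best cases.

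Several stronger readings are tempting, and the document does not support them:

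- **That the strata are faulty.** Stratifying on the count recovers little, and there are already 24 cells for 170 children.
- **That chance imbalance biases the comparison.** Randomisation covers it, and the simulated type I error is close to nominal.
- **That the plan reports an attenuated hazard ratio.** It states no hazard ratio at all. Marginal and conditional hazard ratios differ when rates vary, and with a true value of 0.6 even the adjusted estimate averaged 0.62–0.64, against 0.63–0.67 unadjusted.
- **That the count was wrongly left out of the factor lists.** Those lists, under Sample size and under the secondary analyses, serve secondary aim 2 (predictors of response to antibiotics), not this outcome.
- **That the count is already in hand.** A third documented episode settles eligibility; the exact total need not be known.

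**Conclusion.** The point holds as a low-priority improvement. The article's only stated analysis of time to next exacerbation yields no between-arm estimate and leaves unused a history that sites must review in any case. The direction of the benefit is consistent across every setting tried. Its size is modest: about 1 to just over 10 points of power in most settings with an accurate count, nearly 14 in the most favourable, and as little as 0.2 when past counts are imprecise and rates change. All of these rest on assumed rates, heterogeneity and hazard ratios that the protocol does not supply.

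The point concerns one secondary outcome. Nothing here touches the primary outcome, PC-QOL or the non-inferiority conclusion.

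**What to change.** - At enrolment, record the actual number of exacerbations in the preceding 18 months, not only that it exceeds two.
- Keep the Kaplan-Meier curves.
- Name as the between-arm estimate for time to next exacerbation a Cox hazard ratio with its confidence interval, from a model with treatment and log(prior count).
- Leave the randomisation strata as they are.

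The cost is one data field, one covariate and one sentence of analysis text. The hazard ratio becomes conditional on past rate, which should be said when it is reported. Adjustment does not deal with the fact that the clock starts at resolution, after randomisation, so that children who leave during treatment may not contribute; the report should state how many children in each arm enter this analysis.

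### Exclusion windows are counted back from study entry, but treatment starts at a later exacerbation, so antibiotics taken just before the treated episode breach no stated criterion

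*Protocol article*

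**What the plan says.** All places are in the protocol article.

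- **Eligibility.** Three exclusions carry a time window. One is "receipt of beta-lactam or macrolide antibiotics within the 3 weeks preceding study entry". The exclusion for severe exacerbation applies "in the 8 weeks immediately prior to study entry". The third is "current or recent (in the 4-months before study enrolment) lower-airway infection" by Pseudomonas.
- **Aims of the study.** Pathogen findings during exacerbations are to be "compared with the findings at enrolment when the children are clinically stable".
- **Intervention and follow-up.** The child's baseline state is one "which for each child will be established at enrolment, prior to any exacerbations". On sequence: "If eligibility is fulfilled, and after informed consent has been obtained, the child will be randomized to one of two arms". On dosing: "At the start of the exacerbation, the child will receive orally" the allocated pair of medications.
- **Randomization, allocation, and blinding.** "Upon enrolment, the child will be assigned to the next unique number on the appropriate stratified list".
- **Recruitment.** Between enrolment and exacerbation there is monthly contact with parents and a review every 3 months. Parents are asked to contact the research nurse when an exacerbation begins.
- **Outcome measures and Statistical analysis.** Additional antibiotic treatment makes a child non-resolved. The primary analysis follows allocation, and a per-protocol analysis is a pre-specified secondary analysis.

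**The concern.** The windows are tied to one date and the treatment to another. A window on recent antibiotics is useful in this trial if it keeps the treated episode free of earlier drug. Here it protects the weeks before enrolment, when the child is well and takes no trial drug. It says nothing about the weeks before the first dose.

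The antibiotic window matters most. If a child has already had a beta-lactam or macrolide for the same illness, or shortly before it, resolution by day 21 depends partly on that earlier drug, whichever arm the child is in. This pulls the two resolution rates together. In a superiority trial that would cost power. In a non-inferiority trial it makes a truly worse treatment easier to pass, and the 20% margin is one that the article itself calls relatively large. The planned look at pathogens and azithromycin resistance as predictors of response would be blurred by the same exposure.

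**Working it through.** The plan states no figure on this point, so there is none to reproduce. The check has three steps.

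**1. The sequence.** Enrolment takes place in a stable state, before any exacerbation. Allocation follows at enrolment. Then comes a wait with monthly contacts and 3-monthly reviews, and the first dose is given at the start of an exacerbation. The article does not define study entry, but reading it as the first dose does not fit this order. I then looked for another rule that closes the gap:

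- The definition of an exacerbation rests on sputum and cough lasting more than 3 days. It has no condition on earlier antibiotics, and those days leave room for an outside prescription.
- The additional-antibiotic rule classifies the outcome. It does not say whether an episode that was already treated may enter.
- The primary analysis by allocation keeps such a child. The per-protocol analysis would not clearly remove the child, who has breached no written criterion.

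**2. How many children the window leaves uncovered.** Inputs: more than two exacerbations in 18 months (Eligibility), so at least 3. Assumption: the wait T from entry to the next exacerbation is exponential with mean m, so P(T > w) = exp(−w/m). Eighteen months is 18 × 365.25/12/7 = 78.3 weeks, and 4 months is 17.4 weeks. The rates of 4 and 6 per 18 months are assumed to give a range.

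| Exacerbations per 18 months | m (weeks) | T > 3 weeks | T > 8 weeks | T > 4 months |
|---|---|---|---|---|
| 3 | 78.3/3 = 26.1 | exp(−3/26.1) = 89% | 74% | 51% |
| 4 | 78.3/4 = 19.6 | 86% | 66% | 41% |
| 6 | 78.3/6 = 13.0 | exp(−3/13.0) = 79% | 54% | 26% |

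For the children in the T > 3 weeks column, the whole of the 3 weeks before treatment lies after entry, where the criterion does not apply.

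**3. What contamination would do.** The article gives no rate of prior antibiotic use, so this is only an illustration. Suppose true resolution is 80% on amoxycillin-clavulanate and 60% on azithromycin, a deficit exactly at the margin. Suppose also that in a fraction f of children earlier antibiotics remove the difference, so that both arms resolve at 80%. The deficit becomes 20 × (1 − f) points. With 85 per arm and the stated one-sided 0.05, the chance of wrongly concluding non-inferiority is Φ(0.20f/SE − 1.645), where SE = √[(0.8 × 0.2 + p(1 − p))/85] and p = 0.60 + 0.20f.

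- f = 0: deficit 20 points, chance 5%.
- f = 5%: deficit 19, SE 0.0684, Φ(0.146 − 1.645) = about 7%.
- f = 10%: deficit 18, SE 0.0682, Φ(0.293 − 1.645) = about 9%.
- f = 20%: deficit 16, SE 0.0678, Φ(0.590 − 1.645) = about 15%.

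**The case against.** **The article is condensed.** Figure 1 and the full protocol are not shown, and either may contain a check at onset. That limits how firmly the point can be put, but does not remove it. The article does not merely leave the time point unstated. It names one, and in a design that allocates first and treats later that time point does not protect the treated episode.

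**Severe episodes are already excluded from treatment.** A reader might infer from the 8-week window that a child whose new episode is itself severe would be treated and counted. The documents do not support that. The Abstract and Study design limit treatment to non-severe exacerbations. What remains is narrow: no check of severity at onset is described, and a recent severe episode between entry and treatment is not covered.

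**The percentages do not measure contamination.** This is right. The 79% to 89% are children whom the window leaves uncovered, not children who took antibiotics. The exponential model is also an assumption, and a history selected for frequent exacerbations may overstate the future rate. That last objection works the other way, however: longer waits would raise the uncovered share.

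**There are partial safeguards.** Trained parents, monthly contacts, a call to the nurse at onset and the outcome rule on additional antibiotics all narrow the route. None of them makes earlier antibiotic receipt a recorded condition of the treated episode.

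**Restricting the primary analysis would conflict with the plan.** This stands too. The article analyses by allocation and expects the primary outcome in all enrolled children, so the remedy should not replace that set.

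**Conclusion.** The point holds for the time anchor. The three windows are counted from entry or enrolment, treatment begins later, and nothing in the text shown re-applies them. The consequence that matters is that episodes with recent beta-lactam or macrolide exposure are admissible as written and would bias the comparison towards non-inferiority.

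Assuming exponential waits with a mean of 3 to 6 months, about 79% to 89% of children would start treatment with none of the preceding 3 weeks covered by the antibiotic window. The size of the bias cannot be stated, because the share with prior antibiotics is not given. The illustration shows only that 5% to 20% affected would raise a 5% error to about 7% to 15%, under the assumptions listed. It would be wrong to conclude that most children are contaminated or that the trial admits severe episodes. The point deserves correction before analysis, subject to what the full protocol and Figure 1 say.

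**What to change.** Reconcile the anchor in Eligibility with the timing in Intervention and follow-up and in Randomization, allocation, and blinding:

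1. State that the plan's own exclusion criteria are also assessed and recorded at exacerbation onset, before the first dose and blind to allocation. The onset call to the research nurse is a natural place for the antibiotic history.
2. Keep the primary analysis by allocation.
3. Use recorded pre-dose receipt of beta-lactam or macrolide antibiotics to define the a priori per-protocol set, and report that result beside the primary one. Because this information precedes the first dose and is collected blind, excluding on it does not disturb the comparability of the arms.

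How an ill child who fails a criterion at onset is managed is a clinical matter for the investigators, and no rule is proposed here.

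The cost is a short checklist at a contact that already exists, though oxygen saturation needs attendance and the article says some children may be unable to attend at onset. The per-protocol set would be somewhat smaller: if 10% were affected (assumed), 17 of 170 would leave it and 153 would remain.
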